## Abstract

**Introduction:**

Post-COVID-19 condition (post COVID, also known as long COVID) is a global public health issue estimated to affect over 100 million people. Common symptoms include fatigue, dyspnoea and cognitive dysfunction (‘brain fog’). Over time, these symptoms have an adverse effect on mental health, physical activity and quality of life (QoL). The condition requires innovative and feasible treatment approaches that can be effective and self-managed. Physical activity is essential for good health; however, aerobic exercise or weightlifting may not be suitable for post COVID patients who experience fatigue or breathlessness. The benefits of yoga include improved flexibility, mobility, body strength and balance. It is also shown to reduce symptoms of fatigue and improve breathing efficiency, mental health and QoL. This study protocol describes the rationale and methods for a randomised controlled trial (RCT) of a yoga-based intervention designed for adults with post COVID.

**Methods and analysis:**

A two-group, parallel, RCT with blinded follow-up assessments. Participants will be randomised with a 1:1 allocation to either a 12-week yoga-based intervention or a 12-week health promotion (active comparison) intervention. In total, 88 participants aged 30–65 years will be recruited and randomised. The primary outcome is health-related QoL (36-item Short-Form). Secondary outcomes are dyspnoea, fatigue, sleep quality, cognitive functions, mental fatigue, depression, anxiety, physical activity, demographic data and physical health measures. Data will be analysed as intention-to-treat basis, using linear mixed modelling. All assessments are conducted at Karolinska Institutet in Stockholm, Sweden. The yoga-based intervention will take place at a yoga studio centrally located in Stockholm city.

**Ethics and dissemination:**

The study is approved by the Swedish Ethical Review Authority, reference number 2023/06518-01. All participants must sign written informed consent before enrolment and are free to withdraw from the study at any point. Key results will be available through research articles and seminars.

**Trial registration number:**

German Clinical Trials Register, DRKS00032837.

STRENGTHS AND LIMITATIONS OF THIS STUDYThe condition-specific yoga programme was codesigned by yoga experts from India and adapted for use in Sweden.Providing compensation for completing participation and keeping routine follow-ups reduces the risk of attrition bias.Giving a similar amount of attention to the control group by health information is reducing the likelihood of a Hawthorne effect.The trial lacks a long-term follow-up assessment.

## Introduction

 Post-COVID-19 condition (post COVID, also known as long COVID) is a threat to public health and individual well-being requiring new treatment options. According to the WHO, the condition begins usually within 3 months from the onset of COVID-19, lasts for a minimum of 2 months and cannot be explained by an alternative diagnosis.^1^ Data from The Swedish Board of Social Affairs and Health (Socialstyrelsen) indicated that between October 2020 and March 2022, approximately 25 000 people in Sweden were diagnosed with post COVID.^2^ The intensity of the condition is heterogenous and related to the varying severity of clinical symptoms.^3^ Common symptoms include fatigue, dyspnoea (breathlessness) and cognitive dysfunction (including ‘brain fog’).^4^ Over time, these symptoms have a detrimental effect on mental health, physical activity levels and overall quality of life (QoL).^5 6^

Physical activity is fundamental for health and well-being; however, aerobic exercise and strength training may not be suitable for individuals with post COVID as common symptoms (eg, fatigue and breathlessness) may hinder participation or exacerbate the symptoms.^7^ Yoga is an increasingly popular activity which is potentially more suitable for this specific condition. The ancient Indian practice of yoga refers to a unity of the body, mind and spirit, with a holistic outlook on health and well-being. The physical benefits include improved flexibility, mobility, core body strength and balance.^8^

To date, there is no single intervention shown to effectively reduce the multidimensional symptoms of post COVID. Although the effects of yoga have not been assessed in those with post COVID, research has shown positive effects in many of the symptoms commonly associated with the condition. Yoga has beneficial effects on the autonomic nervous system and immune response, as well as contributing to hormonal changes associated with positive mood states.^9^ Additionally, yoga is shown to improve heart rate variability, which is considered a proxy marker for autonomic nervous system regulation and cardiovascular health.^10^ Decreases in chronic physiological stress through yoga may partly explain the positive effects of yoga on anxiety^11^ and cognition.^12^ Furthermore, recent meta-analyses indicate that yoga practice is associated with improvements in fatigue,^13^,^15^ depression and anxiety^11 16^ and sleep quality^17^ when compared with control conditions. It has been suggested that the health benefits of yoga may be mediated by improved sleep quality.^18^ Experiencing extreme fatigue and impaired sleep can have detrimental effects on cognitive abilities and concentration, and often lead to a reduction in health-related QoL (HR-QoL).^19^ Yoga is also shown to help reduce dyspnoea in chronic obstructive lung disease and related conditions.^20^

Post COVID is an emerging threat to health, estimated to affect more than 100 million people globally.^21^ Yoga, with its interdisciplinary approach of physiological and psychological mechanisms, may prove to be a valuable tool for holistic well-being and recovery in the aftermath of the pandemic.^22 23^

### Rationale

Current approaches to the treatment and management of post COVID are largely symptom based. There is a need to develop lifestyle-based approaches that will improve heterogenous symptoms and can be self-managed and maintained with limited supervision. Yoga has the potential to ease the symptoms and sequelae of post COVID. However, trials are needed to determine its effectiveness. Findings will support clinicians in making evidence-informed treatment decisions. Our study targets middle-aged adults, as this group are disproportionately affected by post COVID and are likely to experience significant morbidity as they age.

To develop a condition-specific yoga programme for post COVID, we have established a collaboration with expert researchers from the Institute of Public Health in Gujarat, India, and the Yoga University, Gujarat. Our international research team includes experts in yoga-based exercise and post COVID research. Through a consensus development process, our expert colleagues have identified postures, awareness practices and breathing techniques most suitable for people with post COVID. The process is described in a forthcoming paper.^24^ These validated methods will be adapted locally in Sweden to optimise the effects of the intervention and minimise adverse events. Concurrently, our Indian collaborators will be conducting a parallel study in India during the same period.

### Study objective

This trial aims to examine the effects of a 12-week yoga intervention on HR-QoL among adults aged 30–65 years diagnosed with post COVID. Results will be compared with a 12-week health promotion control group.

#### Research questions

What are the effects of a 12-week yoga intervention compared with a health promotion intervention on HR-QoL in adults aged 30–65 years with post COVID?What are the effects of yoga on secondary health outcomes, including fatigue, sleep quality, dyspnoea, cognition (including ‘brain fog’) and mental health?Is sleep quality a mediating factor in the relationship between yoga practice and HR-QoL?

#### Hypotheses

We hypothesise that (1) compared with a health promotion intervention, participation in a 12-week yoga intervention will be associated with improvements in HR-QoL. We also hypothesise that (2) participation in a 12-week yoga intervention will have positive effects on all secondary health outcomes. Furthermore, we hypothesise that (3) sleep quality mediates the relationship between yoga and improved HR-QoL.

## Methods and analysis

### Trial design

We propose an open-label, two-group parallel randomised controlled trial (RCT) with blinded follow-up assessments (see participant flowchart for parallel design following Consolidated Standards of Reporting Trials guidelines^25^ in figure 1). Participants will be randomised to one of the two conditions: (1) a 12-week supervised yoga programme or (2) a 12-week health promotion (active comparison) intervention. Both interventions are complementary to usual care (ie, ongoing treatment for post COVID recommended or prescribed by a physician). This study protocol follows Standard Protocol Items: Recommendations for Interventional Trials 2013, recommended guidelines for a clinical trial protocol.^26^

**Figure 1 F1:**
[figure not shown]
Participant flowchart for parallel design based on the CONSORT guidelines^25^ for transparent reporting of trials. CONSORT, Consolidated Standards of Reporting Trials; GP, general practitioner; PSQI, Pittsburgh sleep quality index; SF-36, 36-item Short Form.

### Study setting

The study will take place in Stockholm County. The trial will be conducted at the department of global public health, Karolinska Institutet. The yoga-based intervention will be undertaken at a yoga studio centrally located in Stockholm with a trained yoga instructor.

### Eligibility criteria

A trained research assistant will perform the eligibility screenings. To be eligible for this study, participants must be between 30 and 65 years of age, have residence in Stockholm County, be fluent in Swedish and give consent to randomisation and participation in the trial. The participants must have a diagnosis of post COVID confirmed by their own physician, be able to attend baseline and follow-up assessments at Karolinska Institutet and respond ‘yes’ to the question ‘have your COVID-19-related symptoms had a negative impact on your quality of life?’.

### Exclusion criteria

Participants who have received intensive care treatment for COVID-19. Participants treated in emergency departments or primary care facilities remain eligible.Physical disability, disease or injury that could interfere with, or be worsened by, yoga practice (eg, paralysis, inability to sit, stand and/or walk, severe pain, glaucoma).Severe cognitive impairment (eg, dementia diagnosis).Extensive surgery during the past year or planned for the coming year.Raised blood pressure≥160 mm Hg systolic or ≥100 mm Hg diastolic (measured objectively in a sitting position) or irregular pulse.Recently diagnosed with, or affected by, serious mental illness (eg, psychosis or bipolar disorder) or indicating acute signs of suicidality (eg, recent, or ongoing thoughts of suicide or self-harm).Diagnosed with post orthostatic tachycardia syndrome.Pregnancy.Advised not to participate in moderate exercise by their doctor (insulin-dependent diabetes will need doctors’ agreement before participating).Currently or recently engaged in regular structured exercise, or already practicing yoga or meditation.Currently taking part in another research study.

### Interventions

#### Yoga

Participants randomised to the yoga group will receive a free 3-month membership to a registered yoga studio centrally located in Stockholm. The studio will offer group yoga classes designed specifically for this project. The classes will be adjusted to the needs of those with post COVID, including symptoms of fatigue and dyspnoea. Participants will be encouraged to attend ≥3 classes per week with a qualified yoga instructor. After attending onsite classes for the first 2 weeks to familiarise themselves with the programme and the instructor, they will have the option to join classes online on occasions where onsite participation is not an option. Attendance and type of participation are taken for each participant in each class. The length of the intervention is consistent with other yoga-based interventions.^27^ The yoga programme has been developed through a consensus development process by our expert collaborators at the Yoga University, India, and consists of postures and breathing techniques suitable for people with post COVID symptoms.^24^ A short description of the programme, which is broadly based on Hatha and Kundalini yoga principles, is available in online supplemental file 1. Physical postures (asanas) included in the programme are gentle shoulder, arm and neck movements, forward bends, gentle supine and sitting twists, aiming to improve flexibility, mobility and core strength, while also facilitating stress reduction.^8 9^ Additionally, several breathing techniques (pranayamas), such as alternate nostril breathing and humming bee breathing, are included, followed by relaxation and meditation techniques, such as focused attention and body awareness. The duration of a class is between 45 and 60 min and consists of a combination of the physical postures followed by breathing and relaxation techniques. Classes are held mid-morning or mid-afternoon and will be delivered by qualified yoga instructors trained by our expert collaborators in India.

#### Health promotion (control)

Participants randomised to the health promotion group will receive fortnightly updates consisting of health promotion information (also for 3 months). A study-specific health promotion web page will be developed and updated with general health information; topics will include healthy eating, nature therapy, social connectedness, sleep habits and substance use (eg, strategies to quit smoking and reduce alcohol intake). Additional content will address post COVID concerns, providing practical guidance on managing fatigue, dyspnoea and ‘brain fog’. The contents will be concise (1–2 pages) and sourced from reliable organisations, including the WHO, and local health promotion agencies. An example of the health promotion content and format is available in online supplemental file 2. Participants will access the web page through a link sent fortnightly via email. To prevent group contamination, no health promotion information will be shared regarding breathing control, stretching or ‘mindfulness’ practices. Participants in the health promotion group will be advised not to take part in yoga, Pilates, tai chi or similar forms of exercise as well as any form of meditation during the 12-week intervention. Part of the rationale for delivering the health promotion to participants regularly is to reduce the likelihood of a Hawthorne effect, that is, to ensure the participants receive a similar level of attention. As an incentive, participants randomised to the health promotion group will receive a complimentary membership to the yoga studio when they attend their postintervention assessment.

#### Measures to maintain adherence

The yoga studio chosen for the intervention is located close to public transport connections. A research assistant will contact each yoga participant by phone every 2 weeks to discuss any adherence-related issues (eg, transport or motivation). Participants will be encouraged to contact the study research assistant if they experience an adverse event, such as pain or injury, related to yoga. A research assistant will conduct a 6-week mid-intervention follow-up (all participants) to assess adherence and adverse events. Yoga participants will complete a weekly exercise diary and attendance will be recorded at the yoga studio.

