#### Follow-up assessments

All participants will be followed up in person at half-time (6 weeks) to discuss progress, adherence and occurrence of any adverse events associated with the intervention. Assessments at 6 weeks will include the SF-36 and the PSQI. Postintervention assessments of all primary and secondary outcomes will be performed at 12+1 weeks, following the same procedure as at baseline (see figure 2). A brief semistructured interview is held at post intervention to gather participant views on the intervention. Postintervention assessments are held at the same time as baseline assessment for each participant.

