### Assessment of harms

Trained research assistants will screen all potential participants and exclude those with health-related problems that might hinder participation or be worsened by yoga. Throughout the study, all adverse events will be reported, evaluated and followed up by a research assistant. Any adverse events needing medical attention will be addressed and referred to appropriate medical professionals. Adverse events will be formally assessed at 6-week follow-up and at post intervention (12+1 weeks) by asking participants if they had experienced any worsening of symptoms, injuries or other adverse efforts during the trial. Participants who report adverse events will be advised to see their general practitioner for further evaluation. All participants will be instructed to contact the study coordinator if any adverse events occur during the intervention. Decisions of participant or study discontinuation based on adverse effects will be made by the principal investigator. Participants can decide to dropout from the study at any given time. The yoga instructors are certified by the Yoga Alliance Guidelines and trained in minimising the risk of injuries and harm.

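### The scope of adverse events is stated inconsistently, and yoga participants have between-visit contact that controls lack, so a comparison of all recorded events could be distorted

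*Protocol article*

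**What the plan says.** Three sections of the protocol article describe how adverse events come to light.

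- **Measures to maintain adherence.** The prompt for self-initiated reports is tied to cause: "Participants will be encouraged to contact the study research assistant if they experience an adverse event, such as pain or injury, related to yoga". The next sentence sets no causal limit: "A research assistant will conduct a 6-week mid-intervention follow-up (all participants) to assess adherence and adverse events". Two contacts are for the yoga arm only: "A research assistant will contact each yoga participant by phone every 2 weeks to discuss any adherence-related issues (eg, transport or motivation"), and "Yoga participants will complete a weekly exercise diary and attendance will be recorded at the yoga studio".
- **Follow-up assessments.** The 6-week visit, for all participants, is held "to discuss progress, adherence and occurrence of any adverse events associated with the intervention".
- **Assessment of harms.** The scope is unrestricted: "Throughout the study, all adverse events will be reported, evaluated and followed up by a research assistant". On timing, "Adverse events will be formally assessed at 6-week follow-up and at post intervention (12+1 weeks"). The question put to participants there concerns any worsening of symptoms, injury or other adverse effect, whatever its cause. All participants, in both arms, are also told to contact the study coordinator about any adverse event.

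Between visits, the Health promotion (control) section describes only a web link emailed every two weeks. The Yoga section encourages at least three instructor-led classes a week.

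**The concern.** Two features combine.

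First, the document does not settle which events count. An event the participant attributes to yoga, an event linked to the allocated intervention, and any event at all are three different things. The second and third are both attached to the same 6-week visit. A causal filter applied by the participant at the point of reporting does not act equally in the two arms. A control participant who receives an emailed link has little that could seem caused by it. A yoga participant with a flare of fatigue may put it down to post COVID and not mention it. The Introduction itself notes that exercise may aggravate symptoms in this condition, so worsening is a harm of particular interest, and one that a lay judgement of cause handles poorly.

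Second, an event mentioned on a yoga-only call falls under the instruction to record all events throughout the study. Controls have no matching contact at which the same event might be mentioned.

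At stake is how the harms table can be read. The Discussion presents yoga as safe and foresees its use in clinical practice, so readers are likely to compare the arms.

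**Working it through.** The document states no adverse event rate, count or safety comparison, so there is no figure to reproduce. The check sets the texts side by side, counts contacts, and then shows by assumption what unequal capture could do.

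**1. The 6-week visit, as described in three places**

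| Section | Events covered at 6 weeks |
|---|---|
| Measures to maintain adherence | adverse events, no causal limit |
| Follow-up assessments | those associated with the intervention |
| Assessment of harms | any worsening, injury or other event |

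Two of the three are unrestricted and one is not. The self-report route differs as well: yoga-related events to the research assistant in one section, any event to the study coordinator in another.

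**2. Contacts per participant over 12 weeks**

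- Formal adverse event questioning: 2 in yoga, 2 in control (6 and 12+1 weeks). Equal.
- Fortnightly calls, yoga only: 12/2 = 6, or 5 if the last coincides with the final assessment.
- Calls plus visits: 5 + 2 = 7 to 6 + 2 = 8 in yoga, against 2 in control.
- In addition, yoga only: about 12 diary entries, and 3 × 12 = 36 classes if attendance is at the encouraged minimum.

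**3. Illustration of unequal contact (all capture values assumed)**

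Let the true event risk p be the same in both arms. Let s be the share captured through routes open to both arms, and e the share of the remainder picked up only through yoga-arm contacts. Then:

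- reported risk in control = p·s
- reported risk in yoga = p·[s + (1 − s)·e]
- ratio = 1 + (1 − s)·e/s, which does not depend on p

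| s | e | Ratio |
|---|---|---|
| any | 0 | 1.00 |
| 0.9 | 0.25 | 1 + 0.1 × 0.25/0.9 = 1.03 |
| 0.7 | 0.25 | 1 + 0.3 × 0.25/0.7 = 1.11 |
| 0.7 | 0.5 | 1 + 0.3 × 0.5/0.7 = 1.21 |
| 0.5 | 0.5 | 1 + 0.5 × 0.5/0.5 = 1.50 |

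With p = 0.3, the spurious difference in the rows with e above 0 runs from 0.3 × 0.1 × 0.25 = 0.0075 (0.8 percentage points) to 0.3 × 0.5 × 0.5 = 0.075 (7.5 points). With 88/2 = 44 per arm, that is 0.0075 × 44 = 0.3 to 0.075 × 44 = 3.3 participants.

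**4. Adding the causal filter**

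If the filter makes shared capture differ by arm, the ratio becomes [sY + (1 − sY)·e]/sC, where sY and sC are the shared-route capture in yoga and control. Take e = 0.25, again as an assumption:

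- Filter bites harder in yoga (sY = 0.5, sC = 0.7): (0.5 + 0.5 × 0.25)/0.7 = 0.625/0.7 = 0.89.
- Filter bites harder in control (sY = 0.7, sC = 0.5): (0.7 + 0.3 × 0.25)/0.5 = 0.775/0.5 = 1.55.

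The same truth can thus appear as an excess or a deficit in the yoga arm. Nothing in the document fixes s, e or the filter.

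**The case against.** The best defence is that Assessment of harms is the governing section and is symmetrical. It asks everyone the same unfiltered question at the same two times, and tells everyone to report any event. The narrower prompt sits in a section on adherence and invites contact; it is not a rule about what is recorded. The calls are described as dealing with matters such as transport and motivation, and the diary as an exercise diary. No section has instructors collecting or passing on events. Statistical methods names no safety comparison, and how events are tabulated is commonly left to the analysis plan.

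Much of this stands, and it rules out stronger conclusions that a reader might infer:

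- **That adverse events are captured far more intensively in the yoga arm.** Formal questioning is equal. Extra capture through calls, diary and classes is a plausible by-product, not a stated procedure.
- **That events will be pooled, giving a biased comparison.** No section says so. The sentence on reporting all events concerns the handling of individual events.
- **That yoga will look falsely harmful by some number of percentage points.** Any such figure comes wholly from assumed capture rates. It is zero if the calls and diary yield nothing, and the causal filter may act the other way.

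What the defence does not remove is the conflict in the text. Follow-up assessments and Assessment of harms describe the same 6-week visit with different scopes, and a member of staff following one would ask a different question from a member following the other. Nor does it remove the contact imbalance: an event mentioned on an adherence call still has to be recorded.

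**Conclusion.** The point holds as an inconsistency in scope together with an imbalance in opportunity. The protocol both restricts adverse events by perceived cause (in two places) and covers all of them (in Assessment of harms). Only the yoga arm has contact with staff between visits: about 7 to 8 calls and visits against 2, before diary and classes. A between-arm comparison of all recorded events could therefore be distorted. Neither the direction nor the size can be determined from the document. The illustrative ratios, 1.00 to 1.50 from extra contact alone and 0.89 to 1.55 in the two filter examples, show only that the effect could be nil or could alter the reading of a small table. They rest on assumed capture shares and an equal true risk. No figure in the protocol is wrong on this point. The correction should be made because it is cheap and removes a filter that the protocol's own harms section contradicts.

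**What to change.** 1. Reconcile Measures to maintain adherence and Follow-up assessments with Assessment of harms, so that any adverse event is elicited regardless of perceived cause and relatedness is judged afterwards. Name one contact point for self-initiated reports in both arms.
2. Record the source of each event: 6-week question, 12+1-week question, self-initiated contact, call, diary or class.
3. Base any between-arm comparison on the identical question put to both arms at 6 and 12+1 weeks.
4. List separately, as descriptive yoga-arm data, events that surface only through yoga-arm contacts.
5. Trial status plans recruitment from January 2024 under a protocol version dated August 2024. If 6-week visits have already taken place, state which wording was used at them.

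The cost is a change of wording and one extra field per event, with no new assessments. The comparative table will hold slightly fewer events, since those known only from yoga-arm contacts move to their own listing.
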